
#### 2.3.2. Follow-Up

Study participants will be followed up for 12 months after enrollment in the study. During this period, detailed records will be maintained for each patient, including the occurrence of new AF episodes and other MACE such as myocardial infarction, stroke, HF, and AF-associated hospitalizations. Any changes in medication will also be documented.

In the follow-up phase, participants will undergo a comprehensive re-evaluation, including a full standard transthoracic echocardiogram and 24-h ECG ambulatory Holter monitoring. The echocardiogram will assess the dimensions and functionality of the LV and LA, along with other parameters such as LVEF, GLS, diastolic indices, and RV function. The 24-h ECG ambulatory Holter monitoring will record continuous ECG data to measure parameters including the total burden of premature atrial and ventricular contractions, episodes of AF, microvolt TWA, HRV indices, and deceleration capacity.

The aim of this follow-up is to assess the feasibility of correlating changes in these echocardiographic and ECG parameters with the recurrence of AF. This will serve as an initial step toward evaluating whether such parameters could potentially predict arrhythmia relapses in a larger study cohort. By examining these associations, the study aims to explore potential factors contributing to AF recurrence and other cardiovascular outcomes, ultimately supporting the development of more personalized treatment strategies for patients with PAF.

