## 2. Methods

### 2.1. Study Design

The PLACEBO (“ParoxysmaL Atrial fibrillation prognosis based on Cardiopulmonary Exercise test data and novel echocardiographic and plasma BiOchemical indices”) trial is a pilot, prospective, observational cohort study designed to explore the feasibility of integrating CPET data, novel echocardiographic indices, and plasma biochemical markers in consecutive patients with PAF for the prediction of AF recurrences. As this is a feasibility study, no specific treatment interventions were prescribed as part of the study protocol. Instead, the study aims to identify potential signals and generate hypotheses for future larger-scale investigations.

The sample size of 80 participants was chosen pragmatically, based on the feasibility of recruitment and data collection within the study’s timeframe and resources. Formal sample-size calculations were not performed, as the primary aim of the study is to assess the feasibility of the proposed methodology and to explore potential predictors of AF recurrence, rather than to test specific hypotheses. This approach aligns with the exploratory nature of pilot studies, aiming to provide preliminary insights into the utility of these diagnostic modalities and establish a basis for future, larger-scale studies.

The study is being conducted at Ippokratio General Hospital in Thessaloniki, Greece. The protocol of the trial is registered at ClinicalTrials.gov (Identifier: NCT05246423) and has been reviewed and approved by the Institutional Review Board (IRB) of Ippokratio General Hospital, as well as by the Aristotle University of Thessaloniki Ethics Committee. Written informed consent was obtained from all participants prior to any study-related procedures. The study is being conducted in accordance with the Declaration of Helsinki and Good Clinical Practice guidelines.

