### 2.4. Outcome Measures

The primary outcome measure is the recurrence of AF within 12 months from enrollment. This will be determined based on available electronic data and through detailed patient interviews during follow-up sessions. Secondary outcome measures will include a variety of clinical and diagnostic indicators, which will be used to evaluate the overall cardiovascular health of and AF progression in participants. These measures will encompass AF-related hospitalizations, types of cardioversions performed, the total burden of premature atrial and ventricular contractions, and episodes of AF recorded during 24-h ECG ambulatory Holter monitoring. Other ECG parameters such as microvolt TWA and HRV indices will also be assessed.

Additional secondary measures will include key performance metrics from CPET such as peak VO_2_ and VE/VCO_2_ slope, as well as echocardiographic indices like LA strain and LV GLS. Plasma biomarkers such as galectin-3, homocysteine, BNP, and hs-cTnI will also be measured to explore their potential role in predicting AF progression. The time to the first recurrence of AF will also be tracked, which may provide valuable insights into factors that could influence the recurrence of AF.

This study aims to assess the feasibility of monitoring and correlating these measures as potential predictors of AF recurrence, ultimately setting the stage for further validation in a larger, more definitive study.

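### Changes in echo and Holter measures are to be correlated with AF recurrence as a step toward prediction, but nothing ensures that the change comes before the recurrence

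*Protocol article*

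**What the plan says.** The protocol article, section 2.4, defines the outcome: "The primary outcome measure is the recurrence of AF within 12 months from enrollment". Section 2.3.2 sets the matching observation period: "Study participants will be followed up for 12 months after enrollment in the study".

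The same section describes the repeat tests: "In the follow-up phase, participants will undergo a comprehensive re-evaluation, including a full standard transthoracic echocardiogram and 24-h ECG ambulatory Holter monitoring". It gives no month and does not tie the visit to a time before a first recurrence. The measures listed for the repeat Holter include ectopy burden, heart-rate variability and AF episodes.

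The purpose follows: "The aim of this follow-up is to assess the feasibility of correlating changes in these echocardiographic and ECG parameters with the recurrence of AF". The next sentence calls this an initial step toward "evaluating whether such parameters could potentially predict arrhythmia relapses in a larger study cohort", and the one after it speaks of exploring factors that may contribute to recurrence.

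Section 2.5 lists linear, logistic and Cox models for AF events. It does not say how a change score would be related to recurrence. It mentions no landmark, no time-updated covariate and no restriction to change before the first event.

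**The concern.** A predictor has to be known before the event it predicts. Here the candidate is a difference between two visits, complete only at the second, while the outcome clock starts at the first. For anyone whose AF recurs between the visits, the order is reversed: the event comes first and the measurement is finished afterwards.

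The recurrence may then explain the measurement. AF itself could alter atrial size, strain, ectopy or heart-rate variability. So could its treatment: section 2.3.2 records medication changes and section 2.4 records cardioversions. For one listed measure no mechanism is needed, because AF episodes on the repeat Holter are recurrences, and correlating them with recurrence is partly true by construction.

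The Introduction gives the study's purpose as finding promising predictors and generating hypotheses for larger studies. Associations produced by recurrence can be strong and can look stable, so they are likely to be carried forward. The safeguards in section 2.5 (multiple imputation, subgroups, alternative outcome models, bootstrap resampling) do not address temporal order. Resampling would only confirm that such an association is reproducible.

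**Working it through.** **Order of events, from the text**

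| Item | Time | Section |
|---|---|---|
| First echo and Holter | baseline | 2.3.1 |
| Recurrence counted | 0 to 12 months from enrollment | 2.4 |
| Second echo and Holter | in the follow-up phase, month not stated | 2.3.2 |
| Change | known only at the second test | follows from the above |

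No section requires the second test to precede the recurrences with which the change is correlated.

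**Illustration of size.** The plan has no figure to reproduce: it gives no event rate, alpha or power, and the sample size was pragmatic ("The sample size of 80 participants was chosen pragmatically, based on the feasibility of recruitment and data collection").

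Inputs:
- n = 80, from section 2.1.
- Assumed: recurrence p = 0.40, so 32 patients with and 48 without; correlation r = 0.8 between baseline and follow-up values without AF; baseline and follow-up SD of 1; recurrence shifts the later value by s = 0.3, 0.5 or 0.8 SD.
- Truth: the measure has no effect on recurrence.

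SD of change within a group = √(2(1 − r)) = √0.4 = 0.632.

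*Case A: every recurrence precedes the repeat test.*
- Standardised difference d = s/0.632 = 0.47, 0.79, 1.26.
- Apparent AUC = Φ(d/√2) = 0.63, 0.71, 0.81.
- Log odds ratio per SD of change = (s/0.4) × √(0.4 + 0.24s²), where 0.24 = 0.4 × 0.6. For s = 0.3: 0.75 × 0.649 = 0.487, OR 1.63. For s = 0.5: 1.25 × 0.678 = 0.848, OR 2.33. For s = 0.8: 2 × 0.744 = 1.488, OR 4.43.
- t-test noncentrality = d × √(32 × 48/80) = d × 4.38 = 2.08, 3.46, 5.54. On 78 degrees of freedom this gives p < 0.05 in 54%, 93% and nearly 100% of studies. Simulation gives about 52% to 54%, 92% and nearly 100%.

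*Case B: half of the recurrences precede the repeat test.*
- Mean difference = s/2. Pooled variance = 0.4 + 0.4 × s²/4 = 0.4 + 0.1s².
- Noncentrality = (s/2)/√(0.4 + 0.1s²) × 4.38 = 1.03, 1.68, 2.57.
- By simulation, p < 0.05 in about 18%, 39% and 70% of studies.

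*Control.* With no shift, or using only change that precedes recurrence, the rate stays at about 5%.

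**Sensitivity to scale.** If s is expressed in SDs of the change score instead, Case A gives 22%, 52% and 89% at 30% recurrence, and 26%, 59% and 94% at 50%. The apparent AUC is then 0.58, 0.64 and 0.71.

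**The case against.** The strongest defence is that this is a hedged pilot. Section 2.3.2 speaks of feasibility and potential prediction, the parameters meant there could be the measures themselves rather than their changes, and Study Limitations disclaims definitive prediction models. That stands against any claim that a consequence of AF will certainly be reported as a predictor. It does not remove the point: the stated comparison is of changes with recurrence, and the text that follows reads it as bearing on prediction and contribution.

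A reader might infer more than the article supports:
- **That the repeat tests come at month 12, or after most recurrences.** No month is given. Some repeat tests may precede a recurrence; nothing requires them to.
- **That a change score will enter the Cox model and condition on the future.** No section says so. Section 2.5 names CPET data, echo parameters and biomarkers in general terms.
- **That listing CPET metrics and biomarkers as secondary measures in section 2.4 is the same error.** These are described only at baseline, so recurrence during follow-up cannot have caused them, and the same section calls the measures potential predictors. It is a labelling matter.
- **That patients who do not return are ignored.** Section 2.5 plans to compare complete-case and multiply imputed results.

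The size of the effect can also be challenged. The recurrence rate, correlation, shift and timing are all assumed, and the article does not say that a self-terminating episode leaves a lasting shift of 0.3 to 0.8 SD. That stands, and the figures are illustrative only.

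**Conclusion.** The point holds in a limited form. The article plans to correlate baseline-to-follow-up change with recurrences counted from enrollment, and to treat the result as a step toward judging prediction, without ensuring that the change comes first. As written, the analysis cannot separate a predictor of recurrence from its consequence, and for AF episodes on the repeat Holter the two coincide.

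The size depends on how many recurrences precede the repeat test and on how far recurrence moves the measure. Under the stated assumptions, the false-predictor rate runs from about 18% (half precede, 0.3 SD) to nearly 100% (all precede, 0.8 SD), against a nominal 5%. If recurrence moves nothing, or none precedes the test, there is no inflation.

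The primary outcome and the analyses of baseline predictors are untouched. This should be fixed before analysis; it does not undermine the study as a whole.

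**What to change.** In section 2.3.2 and the analysis plan:

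1. Confine prediction claims to baseline values. Alternatively, use change measured up to a landmark visit in patients still free of recurrence, counting only later first recurrences, or a time-updated covariate that takes effect only from its measurement.
2. State when the re-evaluation takes place. If it falls at the end of the 12 months, no later recurrences remain in the window and only baseline prediction is possible.
3. Exclude AF episodes on the follow-up Holter from the candidate predictors.
4. Analyse whole-period change as an outcome: regress the follow-up value on recurrence (yes/no) and the baseline value, and describe the result as remodelling associated with recurrence.

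The same data serve and no new measurement is needed. The study gives up the claim that whole-period change predicts relapse. A landmark analysis also uses fewer events: with the assumed 40% recurrence (32 of 80) and half of it before the landmark, 16 events remain among 80 − 16 = 64 patients.

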### 2.4. Outcome Measures

The primary outcome measure is the recurrence of AF within 12 months from enrollment. This will be determined based on available electronic data and through detailed patient interviews during follow-up sessions. Secondary outcome measures will include a variety of clinical and diagnostic indicators, which will be used to evaluate the overall cardiovascular health of and AF progression in participants. These measures will encompass AF-related hospitalizations, types of cardioversions performed, the total burden of premature atrial and ventricular contractions, and episodes of AF recorded during 24-h ECG ambulatory Holter monitoring. Other ECG parameters such as microvolt TWA and HRV indices will also be assessed.

Additional secondary measures will include key performance metrics from CPET such as peak VO_2_ and VE/VCO_2_ slope, as well as echocardiographic indices like LA strain and LV GLS. Plasma biomarkers such as galectin-3, homocysteine, BNP, and hs-cTnI will also be measured to explore their potential role in predicting AF progression. The time to the first recurrence of AF will also be tracked, which may provide valuable insights into factors that could influence the recurrence of AF.

This study aims to assess the feasibility of monitoring and correlating these measures as potential predictors of AF recurrence, ultimately setting the stage for further validation in a larger, more definitive study.

### 2.5. Statistical Analysis

Data will be analyzed using appropriate statistical methods to evaluate the prognostic significance of CPET data, echocardiographic parameters, and plasma biomarkers. Descriptive statistics will be used to summarize quantitative and qualitative variables and to provide insights into baseline characteristics. Univariable and multivariable analyses will be performed to assess the association between these variables and the recurrence of AF, as well as related adverse outcomes. Various statistical models will be considered, including the following:Linear regression for the number of AF events during follow-up.Binary logistic regression for the occurrence of AF relapse during follow-up.Cox proportional hazards model for the time to an AF event during follow-up.

Given that the study population consists of generally healthy individuals without major comorbidities, the presence of significant confounders is expected to be minimal. However, to ensure robustness, multivariable models will include adjustments for relevant baseline clinical and demographic characteristics if such is deemed statistically or clinically important.

Sensitivity analyses will be conducted to assess the impact of missing data and potential biases. In particular, the missing data will be replaced, when appropriate, using targeted imputation techniques. The results using complete case analyses versus analyses based on multiple imputation will be compared, and the changes that are caused by the missing data will be evaluated. Subgroup analyses will be performed, stratified by key clinical variables (e.g., AF duration, CPET performance, and echocardiographic indices) to explore the consistency of findings across different patient profiles and possibly detect related bias. To further address bias, different modeling strategies will be considered to evaluate AF events during follow-up as already mentioned, including linear regression (targeting the number of AF events), binary logistic regression (targeting the occurrence of AF–Yes/No), and Cox regression (targeting the time to AF event). Nonparametric methods such as decision trees may be also employed. By using alternative model choices to assess AF events during follow-up, a broader understanding of the impacting factors will be achieved. Multicollinearity will be assessed and addressed in all multivariable analyses. Additionally, bootstrap resampling will be used by repeatedly performing model fitting on random subsets of data to assess stability.

For all models, the necessary assumptions will be evaluated and appropriate adjustments will be made. A combination of these analytical approaches will enhance the understanding of the data and improve the robustness of the study findings.

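### Linear regression is named for the number of AF events, a count, so its intervals are unreliable when a predictor truly matters

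*Protocol article*

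**What the plan says.** Section 2.5 introduces its models with "Various statistical models will be considered, including the following". The first entry is "Linear regression for the number of AF events during follow-up"; the other two are logistic regression for relapse and a Cox model for time to an AF event. The sensitivity-analysis paragraph of the same section returns to "linear regression (targeting the number of AF events", set beside the other two as alternative strategies. Neither place mentions a count model, an event rate or an offset.

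Two further statements in section 2.5 bear on the point. The section closes with "For all models, the necessary assumptions will be evaluated and appropriate adjustments will be made", without naming an alternative model. It also says that "bootstrap resampling will be used by repeatedly performing model fitting on random subsets of data to assess stability", which is a stability check and not a source of confidence intervals.

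Section 2.3.2 plans 12 months of follow-up for everyone. Section 2.4 makes AF recurrence within 12 months, a yes/no outcome, the primary measure. In section 2.1, "The sample size of 80 participants was chosen pragmatically" and "Formal sample-size calculations were not performed". The article gives no expected event rate, share of patients without events, or dropout rate.

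**The concern.** The number of AF events is a non-negative integer. Ordinary linear regression treats it as a continuous variable with the same error variance at every value of the predictor. For counts, the variance moves with the mean. The assumption therefore fails exactly when a predictor is related to the event rate, which is what the study is looking for. This is known from the type of outcome before any data arrive.

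The study is meant to pass promising predictors, with effect sizes, to a larger study. If the intervals around real effects are wrong, the precision reported for the most interesting predictors is wrong too. A straight line can also give negative expected counts. And with no term for time observed, a patient lost early with no events counts the same as one followed for 12 months with no events.

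**Working it through.** **Inputs.** From the article: n = 80, linear regression for the count, planned follow-up of 12 months. Assumed, because the article gives none: mean 0.5 to 2 events per year, negative binomial dispersion k from 0.35 to 5 (smaller k means more over-dispersion), rate ratio 1.0 to 2.0 per SD of the predictor, early dropout 0 to 20%. The article states no figure to reproduce. One predictor is examined at a time.

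**Step 1: variance of the count.** Var(Y) = m + m²/k. With k = 0.5, a mean of 0.7 gives 0.7 + 0.49/0.5 = 1.68, and a mean of 1.4 gives 1.4 + 1.96/0.5 = 5.32. Doubling the rate roughly triples the variance (5.32/1.68 = 3.2).

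**Step 2: binary predictor.** Linear regression uses the pooled variance s² = [(n₁-1)V₁ + (n₀-1)V₀]/78 and the squared standard error s²(1/n₁ + 1/n₀). The true variance of the difference is V₁/n₁ + V₀/n₀. Group 1 has the higher rate.

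- Groups of 40 and 40: s² = 3.50; model 3.50 × 0.05 = 0.175; true (5.32 + 1.68)/40 = 0.175. SE ratio 1.00; simulated coverage 94.0%.
- 20 patients with the higher rate, 60 with the lower: s² = (19 × 5.32 + 59 × 1.68)/78 = 2.567; model 2.567 × 0.0667 = 0.171; true 0.266 + 0.028 = 0.294. SE ratio √(0.171/0.294) = 0.76; simulated coverage 85.9%, too narrow.
- 60 with the higher rate, 20 with the lower: s² = (59 × 5.32 + 19 × 1.68)/78 = 4.433; model 0.296; true 0.089 + 0.084 = 0.173. SE ratio √(0.296/0.173) = 1.31; simulated coverage about 98%, too wide.

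**Step 3: continuous predictor.** The mean is m·exp(bx - b²/2) with x standard normal, so the best linear slope is m × b; for m = 1 and rate ratio 1.5 it is ln 1.5 = 0.405. Coverage of that slope by the nominal 95% interval (20,000 runs each):

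| mean, k | rate ratio 1.0 | 1.5 | 2.0 |
|---|---|---|---|
| 0.5, 0.5 | 95.1% | 89.7% | 80.0% |
| 1, 0.4 | 95.2% | 88.6% | 77.4% |
| 2, 0.5 | 95.0% | 87.9% | 76.9% |
| 1, 5 | 94.9% | 91.8% | 82.9% |

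With mean 1.2 and k from 0.35 to 1.0, coverage is 85-87% at 1.65 and 77-79% at 2.0. With a right-skewed predictor, as a biomarker on its raw scale might be, it is 62-74% at 1.5 and 34-42% at 2.0, but still about 95% with no association.

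Robust (HC3) standard errors on the linear model help only in part. With the normal predictor they give 89-94% at 1.5 and 83-91% at 2.0.

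**Step 4: negative fitted counts.** With the normal predictor, about 1-2% of fitted values are below zero at 1.5 and about 7% at 2.0.

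**Step 5: unequal follow-up** (mean 1, k = 0.5, rate ratio 1.5, true slope about 0.405).

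- Dropout of 10% or 20% unrelated to the predictor gives 0.385 or 0.363, a loss of 5% or 10%.
- Dropout related to the predictor gives 0.335 or 0.287, a loss of 17% or 29%.
- With no true association, predictor-related dropout gives a false slope of about -0.03 or -0.05.
- With complete follow-up there is no such bias.

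**Step 6: power.** With mean 1.2, k = 0.35 and rate ratio 1.65, power is 52% for linear regression and 57% for negative binomial regression.

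**The case against.** The strongest defence is that the list is open, assumptions will be checked and adjustments made, and the count is not the primary outcome. Section 2.4 does not list the 12-month number of episodes as an outcome at all, only episodes seen on Holter. No sample size or primary conclusion rests on this regression. This stands, and it lowers the severity. It does not remove the point: linear regression is the only regression tied to the count, it is named twice, and no alternative is given for a violation that is foreseeable.

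Three stronger readings are tempting, and the article does not support them.

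- A reader might infer that the intervals will always be too narrow because the counts are skewed with many zeros. They will not. With 40-71% zeros and no association, coverage is 94.9-95.5%, so these features alone do not inflate false signals. For a binary predictor the intervals can be too wide.
- A reader might take it as given that most patients will have no events. The article reports no event distribution.
- A reader might conclude that the plan ignores follow-up time. That is true of this one model only. The Cox model uses time, the planned 12 months is common to all, and missing data are to be examined by multiple imputation. The gap matters only if some patients leave early.

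The loss of power is also small in the scenario computed.

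**Conclusion.** Wrong as written; should-fix. Linear regression is a poor named choice for this outcome, and the error shows where an association exists. At n = 80 with over-dispersed counts and a normally distributed continuous predictor, nominal 95% intervals cover about 85-90% at a rate ratio of 1.5-1.65 per SD and about 77-80% at 2.0. Nearly Poisson counts (k = 5) do somewhat better, at 92% for 1.5 and 83% for 2.0; skewed predictors do worse. For binary predictors the error goes in either direction.

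All of these figures depend on the assumed event rate, dispersion and log-linear effect. The qualitative conclusion depends only on the variance changing with the mean. A must-fix grade would overstate the matter, since the analysis is exploratory and supports a binary primary outcome for which logistic regression is already named.

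**What to change.** In both places in section 2.5, replace linear regression for the number of AF events with negative binomial regression: log link, log of observed follow-up time as offset, results as rate ratios with 95% confidence intervals. If the dispersion parameter does not converge, fall back to Poisson or quasi-Poisson regression with robust standard errors. That fallback is second best, because robust standard errors can themselves be too small with 80 patients and strongly over-dispersed counts; a small-sample correction is advisable.

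The cost is a change of wording plus the date on which each patient's observation ended. No new measurements are needed. The one downside is that effects are read as rate ratios and no longer as differences in mean number of events.

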### 2.2. Participants

Participants in the study were adults aged 18 years and older, diagnosed with PAF, and in sinus rhythm at the time of baseline evaluation. Eligible participants were required to undergo CPET and comply with follow-up requirements.

PAF was defined according to the ESC 2020 and 2024 Guidelines as AF episodes that terminate spontaneously or with an intervention within 7 days, typically within 48 h [4,19]. Patients with persistent or permanent AF were excluded to maintain a homogeneous study population. To ensure accurate classification, all patients had a documented time of AF onset, as reported from one of the following sources:Hospitalization with a recorded AF episode and documented termination.Outpatient or patient visit to the Emergency Department with a definite AF onset time, either self-reported or confirmed via surface electrocardiogram (ECG) or 24-h ECG Holter monitoring.AF episode terminated in-hospital, either spontaneously, pharmacologically, or electrically.

Additionally, all participants underwent 24-h ambulatory ECG Holter monitoring at baseline to confirm sinus rhythm and assess AF burden. Medical records and prior ECG documentation were reviewed to validate AF classification and exclude cases of persistent AF.

To assess the duration of AF, data were collected regarding the time since the first documented AF diagnosis based on medical records and patient history. While the exact onset date was not necessarily available, disease duration was recorded as a key variable to assess AF burden and progression.

The inclusion criteria were meeting these conditions and being capable of providing written informed consent. The exclusion criteria consisted of structural cardiomyopathy, congenital heart disease, permanent AF, recent acute coronary syndrome (within the last month), heart failure (HF) with reduced ejection fraction, end-stage renal disease, autoimmune diseases, active malignancies, uncontrolled thyroid disease, recent surgery (within the last 2 months), poor echocardiographic windows, uncontrolled systemic hypertension, prior catheter ablation for AF, and pregnancy. Patients unable to comply with the study schedule or provide informed consent were also excluded.

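### Agreement between complete-case and multiple-imputation results cannot rule out bias from outcome loss that depends on AF recurrence, so the comparison does not measure what missing data changed

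*Protocol article*

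**What the plan says.** Section 2.5 (Statistical Analysis) announces sensitivity analyses for missing data and possible biases. Missing values are to be imputed where suitable. The one comparison it names for missing data is that "results using complete case analyses versus analyses based on multiple imputation will be compared", and it says what this delivers: "the changes that are caused by the missing data will be evaluated". The statement covers all missing data and is not limited to the outcome.

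Section 2.4 sets the outcome: "The primary outcome measure is the recurrence of AF within 12 months from enrollment". On ascertainment it says: "This will be determined based on available electronic data and through detailed patient interviews during follow-up sessions". Section 2.5 lists for this outcome "Binary logistic regression for the occurrence of AF relapse during follow-up", together with a Cox model for time to recurrence and a linear model for the number of events.

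Section 2.1 fixes the sample at 80 on pragmatic grounds. The article gives no expected dropout rate and no expected recurrence rate.

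**The concern.** The difference between a complete-case and an imputed result shows how far two analyses lie from each other. It does not show how far either lies from the result that full data would have given. The two quantities coincide only if the imputation model is right, and standard imputation assumes that, given the variables in the model, loss does not depend on the missing value itself.

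That assumption is open to doubt for this outcome. Recurrence is learned from existing electronic data and interviews, so whether it is captured may depend on where, or whether, the patient sought care. Patients with recurrence might be lost because they are treated elsewhere, or retained because symptoms bring them back.

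The pilot is meant to pick out predictors for a larger study. A predictor whose association was weakened by selective loss could look weak in both analyses, be reported as robust to missing data, and be dropped.

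**Working it through.** The article has no power, event or dropout figure to reproduce. From the article: N = 80, a binary 12-month outcome, logistic regression, and complete case versus multiple imputation. Recurrence near 40%, all loss rates, and a true log odds ratio of 0.5 per SD of one predictor are assumptions.

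**1. Bounds on the recurrence risk.** Let k outcomes be missing and e recurrences be observed. Complete case gives e/(80 − k). The lower bound (none of the lost recurred) is e/80, and the upper bound (all recurred) is (e + k)/80.

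For k = 12 and e = 27:
- complete case: 27/68 = 39.7%
- imputation at the observed rate adds 12 × 27/68 = 4.8 expected recurrences: (27 + 4.8)/80 = 39.7%
- bounds: 27/80 = 33.8% and 39/80 = 48.8%

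Other loss rates, with about 40% observed recurrence:

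| Missing | Observed | Complete case | Bounds |
|---|---|---|---|
| 4 (5%) | 30/76 | 39.5% | 37.5% to 42.5% |
| 8 (10%) | 29/72 | 40.3% | 36.3% to 46.3% |
| 16 (20%) | 26/64 | 40.6% | 32.5% to 52.5% |

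**2. What selective loss does to the logistic model.** Among observed patients, the odds of recurrence equal the true odds × (retention in recurrers ÷ retention in non-recurrers).
- Loss of 30% in recurrers and 10% in others: the factor is 0.7/0.9 = 0.78 at every predictor value. Only the intercept moves, and the odds ratio is unaffected. The risk is not: with a true risk of 40.5%, complete case expects 0.405 × 0.7 / (0.405 × 0.7 + 0.595 × 0.9) = 34.6%.
- Loss of 40% in recurrers with above-average predictor values and 10% in everyone else: the factor is 0.6/0.9 = 0.67 above the mean and 1 below it. The slope is flattened, so the odds ratio is biased.

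**3. Simulation.** Logistic analysis with one standardised predictor and 20 proper imputations; 1,500 runs at N = 80. Overall loss was 18% to 20%.

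| Loss depends on | Imputation model | Quantity | Full data | Complete case | Imputation |
|---|---|---|---|---|---|
| Recurrence only | analysis covariate | risk | 40.5% | 34.5% | 34.9% |
| Recurrence only | analysis covariate | log OR | 0.521 | 0.524 | 0.523 |
| Recurrence and predictor | analysis covariate | log OR | 0.526 | 0.353 | 0.354 |
| Recurrence and predictor | plus auxiliary that predicts recurrence | log OR | 0.439 | 0.258 | 0.287 |
| Predictor only | analysis covariate | log OR | 0.530 | 0.543 | 0.543 |
| Auxiliary and predictor | plus that auxiliary | log OR | 0.373 | 0.216 | 0.369 |

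In row 1 the bias is about 6 points and the methods differ by 0.4. In row 3 the log odds ratio loses 1 − 0.353/0.526 = 33%, while the two methods differ by 0.022 on average against a standard error of 0.28. At N = 2,000 (150 runs) row 3 becomes 0.497, 0.327 and 0.327, so the pattern is not small-sample noise. In row 4 the auxiliary recovers 0.029 of a 0.181 bias. In row 6 the comparison does reveal the bias and imputation removes it.

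**4. Other analyses in section 2.5.** The subgroup analyses, alternative models and bootstrap all use the same observed outcomes. The Cox model can treat lost patients as censored, but that needs censoring unrelated to recurrence, which is the same kind of assumption. None of these analyses varies it.

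**The case against.** Four points on the other side have weight.

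- **The comparison covers all missing data.** A reader might infer that the missing values will mainly be outcomes, since section 2.2 says "Eligible participants were required to undergo CPET and comply with follow-up requirements" and excludes poor echocardiographic windows. The documents do not establish this. Individual CPET, strain, right-heart and Holter measures and assayed biomarkers can be missing, as can the follow-up echocardiogram and Holter data in a patient whose recurrence status is known. For missing predictors, comparing the two analyses can be informative. This stands.
- **The comparison is not blind in every case.** A reader might infer that it can never show bias from missing outcomes. Row 6 of the simulation shows otherwise when auxiliary variables explain the loss, and the article does not say that the imputation is restricted to the analysis covariates. This stands.
- **Predictor effects need not be biased.** A reader might infer that any recurrence-dependent loss distorts them. For the planned logistic model it does not, unless loss also varies with the predictor. This stands, and it matters because associations are the main target.
- **Imputation detail belongs in a statistical analysis plan.** The imputation model, and even a tipping-point analysis, may be set out in a document not shown. Their absence from the article is therefore not the fault. This stands too, but it does not reach the point made here, which concerns the meaning that section 2.5 itself gives to the comparison.

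**Conclusion.** The point holds in a limited form. Section 2.5 states that a complete-case versus imputation comparison evaluates what the missing data changed. Under standard imputation it shows only sensitivity within the missing-at-random assumption. Agreement cannot rule out bias from recurrence-dependent loss: in the recurrence risk always, and in the logistic odds ratio when loss also varies with the predictor.

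The size is unknown, because no dropout rate is given. Under the assumed loss rates, the shared bias was about 6 points in the risk, or about one third of the log odds ratio, with almost no difference between the two analyses. At 5% loss the risk bounds span only 5 points; at 20% they span 20. The consequence is modest, because the article presents the study as exploratory and hypothesis-generating.

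**What to change.** 1. Keep the comparison, and include in the imputation the available variables that may predict both loss and recurrence, such as baseline measures and recorded medication changes.
2. Add a delta-adjusted analysis of the primary outcome, labelled exploratory. Shift the imputed log-odds of recurrence in lost patients over a stated grid, add the all-recurred and none-recurred bounds, and report the recurrence risk and the main odds ratios across it. The grid must be wide enough. Loss of 30% v 10% implies an odds ratio for recurrence in lost versus observed patients of (0.3/0.1)/(0.7/0.9) = 3.9. Loss of 40% v 10% implies (0.4/0.1)/(0.6/0.9) = 6. Because the odds ratio is at risk when loss varies with the predictor, let the shift also differ between high and low values of the predictor under study.
3. Reword section 2.5 to say that the comparison shows sensitivity under missing at random and does not measure the effect of the missing data.
4. Report the number of missing outcomes beside the results.

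The cost is one more analysis on data already held. The downside is that the reported uncertainty becomes wider.
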